##### Secondary Outcomes

Mixed-design analysis of covariance will be conducted within the 2 intervention groups to examine whether time spent engaging with the app content serves as a covariate influencing intervention outcomes.

In-app user feedback collected through the CORTO method will be deductively coded following the process outlined by Saldana [91], using the 4 overarching categories proposed by Lukka et al [82]—(1) contextual use, (2) interaction-elicited emotional experience, (3) usability, and (4) technical issues—as a guiding framework. More detailed subdomains will be explored within each category.

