**Methods:**

Consenting individuals (target N=60) who meet the inclusion criteria (self-reporting problems with repetitive negative thinking) will be randomly assigned to 1 of 4 conditions: (1) intervention with therapist support and daily sampling, (2) intervention without support and with daily sampling, (3) partial intervention (emotion validation EMI only) with daily sampling, or (4) control (daily sampling only). The intervention consists of a series of modules delivered over 4 weeks, with assessments conducted before and after intervention, and again at 1-month follow-up (plus an additional 3-month follow-up for intervention participants). Data will be collected both through online self-report assessments and via the app itself. The potential of the EMI to modify the maladaptive feature of repetitive negative thinking will be assessed using mixed-design ANOVA, while the links between avoidance-mood and rumination-mood, in terms of the moderating effect of trial condition, will be evaluated using multilevel models. These will be assessed as primary outcomes. Secondary outcomes are the effects of a supporting therapist on postintervention outcomes in the intervention groups, and time spent using the app as a measure of engagement (analyzed using the mixed-design analysis of covariance). Compliance will be defined as completing both of the first 2 weeks of intervention content in full, and 5 out of the 6 exercises from weeks 3 and 4. Additionally, the study will control for both the amount of time spent in the app and the length of responses to open-ended questions.

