#### Development, Content, and User Evaluations

The development of the app was undertaken by a multidisciplinary team of active RFCBT practitioners; research psychologists with experience in transdiagnostic processes, digital mental health interventions, and user experience; and experienced developers of digital tools from the Polish-Japanese Academy of Information Technology.

The intervention comprises psychoeducational content based on RFCBT, an effective intervention for maladaptive rumination [86]. The reduction of EA is targeted through (1) the provision of a functional analysis of rumination to identify the triggers and functions of this process (a classical component of RFCBT), and (2) the modification of beliefs concerning negative emotions and their experience [87,88]. Previous research on the use of RFCBT has also found it to be an effective rumination intervention when delivered in digital contexts [89].

Intervention content was initially developed by members of our team with expertise in RFCBT. The content is divided into 4 weeks, with the first 2 weeks containing several individual modules targeting specific learning outcomes (eg, learning about the function of emotion, learning about the avoidance of emotions). The delivery of informative content is interspersed with several small exercises in different formats (multiple choice or open-ended text entry). Weeks 3 and 4 provide users with a series of exercises designed to consolidate learning and offer an opportunity for users to apply the psychoeducational content to their personal lives. Individual modules are designed to take no longer than 10-15 minutes to complete. The app content is delivered linearly, with subsequent weeks unlocking only once previous ones are fully completed. On each day of the intervention, all users are required to complete an emotion valuation question. All user inputs when completing app content are stored remotely and securely via Firebase (Google LLC), accessible only to the research team and solely for analysis purposes. In addition to user inputs and assessment outcomes, the time taken to complete app content and assessments is also recorded to observe the time burden caused by app use. A summary of the app intervention content can be found in Table 1.

**Table 1 table1:** Overview of intervention content.

Week, module, and module name				Module objectives

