### Statistical Analysis

#### Data Exclusion

Compliance will be defined as the completion of both the first and second weeks of the intervention content in full, along with at least 5 out of 6 exercises from weeks 3 and 4. For EMA, a compliance threshold of 80% will be used, consistent with previous research using EMIs in adult populations [90]. Additionally, the study will control for time spent within the app and the length of responses to open-ended questions.

In addition to the aforementioned compliance measures, participants who fail both attentional checks embedded within the assessments will be excluded from analyses.

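### On the natural reading of the compliance exclusion, the engagement analysis is left with almost no variation in content completed and can hardly detect an effect of doing more of the programme

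*Protocol article*

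**What the plan says.** The abstract of the protocol article (Methods) lists as a secondary outcome "time spent using the app as a measure of engagement". The Secondary Outcomes section fixes model and arms: "Mixed-design analysis of covariance will be conducted within the 2 intervention groups", with the aim "to examine whether time spent engaging with the app content serves as a covariate influencing intervention outcomes".

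The Data Exclusion section sets the compliance rule: "Compliance will be defined as the completion of both the first and second weeks of the intervention content in full". The second part of the rule asks for no fewer than five of the six later exercises. On attention checks the section then says: "In addition to the aforementioned compliance measures, participants who fail both attentional checks embedded within the assessments will be excluded from analyses". The section on development, content and user evaluations says that the same content rule decided who was analysed in the feasibility study.

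That section also describes the content as linear, each week opening only after the one before is finished. Of the timer it says "the time taken to complete app content and assessments is also recorded to observe the time burden caused by app use". Table 1 lists the modules.

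**The concern.** The question is whether people who engage more with the programme do better. The compliance rule selects on engagement itself. If it also defines the set for this analysis, those with low engagement are removed before the question is asked, and those who stay have all seen nearly the same content. Minutes can still differ among them, but for a first pass through fixed content those differences come mainly from reading and typing pace, length of answers, or a screen left open.

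A null result would then say almost nothing about engagement, yet it would be reported as the answer to a named secondary outcome.

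**Working it through.** **Plan's own figure.** The engagement analysis has none. The overall sample size of 60 is reproduced for a within-between interaction with 4 groups, 3 occasions, f = 0.25, correlation 0.5, alpha 0.05 and power 0.95 (achieved 0.954); only the groups, the occasions and a medium effect are stated. With equal allocation the two intervention arms hold 60 × 2/4 = 30 people. If recruitment is doubled, as Participants and Power Analysis intends, they hold 120 × 2/4 = 60.

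**Step 1: content completed by a complier.** Table 1 gives 4 + 4 + 4 + 3 = 15 modules in weeks 1 to 4 (week 0 left out). Three of the six exercises are in week 3 and three in week 4. Week 4 opens only when week 3 is complete, so a complier can miss at most one week 4 exercise. Content completed is 14/15 = 93% or 15/15 = 100%.

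**Step 2: variation lost.** Assume 40% comply (the feasibility study analysed 21/55 = 38%), half of them at 14/15, and non-compliers spread evenly from 0 to 0.9.

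- Compliers only: SD = (1/15)/2 = 0.033.
- Everyone: the compliers' mean is 0.967 and the non-compliers' 0.45. Variance = 0.4 × 0.033² + 0.6 × 0.9²/12 + 0.4 × 0.6 × (0.967 − 0.45)² = 0.0004 + 0.0405 + 0.0641 = 0.105, so SD = 0.32.

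The filter cuts the spread of content completed about tenfold.

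**Step 3: best case inside the filter.** Suppose full against no content changes the outcome by 1 unit, with residual SD 0.8. Compliers differ by at most 1/15 = 0.067 units. With 0.4 × 60 = 24 compliers split 12 and 12, the standard error is 0.8 × √(1/12 + 1/12) = 0.33, and the expected ratio is 0.067/0.33 = 0.20. Even a perfect measure of content could not show the effect here.

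**Step 4: simulation under the same assumptions.** 60 people in the two arms, log-normal pace with log SD 0.5, change driven by content completed only.

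| Measure and set | Detected |
|---|---|
| Minutes, compliers only | about 5% |
| Minutes, filter lifted | about 25 to 66% |
| Content completed, filter lifted | about 61 to 87% |

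The low ends belong to 40% of non-compliers giving outcomes, the high ends to all of them doing so; the minutes range also depends on whether minutes are logged. A repeat run moved these figures by at most about four points. Lifting the filter is what recovers most of the lost information; adding content completed recovers more.

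**Step 5: which term answers the question.** Over pre, post and follow-up, the covariate's average effect includes a pre score that app use cannot alter. A true effect of −0.3 SD at both later occasions is estimated as (0 − 0.3 − 0.3)/3 = −0.20. Simulated rejection rates with n = 30 and correlation 0.5 between occasions:

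| Assumed truth | Average effect | Covariate × occasion | Later scores adjusted for baseline |
|---|---|---|---|
| Time tied to level (0.3 SD per SD), no effect on change | 46% | 5% | 17% |
| No tie to level, effect −0.3 SD | 24% | 35% | 56% |

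Covariate × occasion keeps its error rate. The baseline-adjusted score has more power, but is not fully protected when app time follows stable severity.

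**The case against.** **Exclusion is not stated outright for this analysis.** This is correct. The only explicit statement of removal concerns failed attention checks. But the compliance rule stands under the heading Data Exclusion, the attention-check sentence is worded as an addition to it, and the same rule was an explicit filter in the feasibility study. Exclusion is the natural reading, though not the only one. If non-compliers stay in, minutes do follow content completed and the main fault falls away.

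**Minutes are more than reading speed.** This also stands in part. The Discussion fears that moving through the content too fast may weaken its impact, some exercises need free text, and the Study Design section measures use during the follow-up month. A module count captures none of this. It is a reason to keep minutes and add content completed, not to replace one by the other.

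**A stronger reading is tempting:** that the planned test averages over the pre score and so will mistake slower or more severe users for an effect of engagement. The documents do not support this. The Secondary Outcomes section names neither the term to be read nor the occasions, and the same model supplies covariate × occasion, which holds about 5% error. Such detail is commonly left to an analysis plan, and no figure in the article links app time with severity.

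**The simulation assumes that only content matters.** It does, so the 5% among compliers is close to built in. That result illustrates the loss of range shown by the module count; it is not a forecast.

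**Conclusion.** The concern holds for the analysis set. If the content-compliance rule is applied here, as the Data Exclusion section naturally reads, the analysis covers people who completed 93 to 100% of the content, and an effect of doing more of the programme is close to undetectable. The module range follows from the article alone. The detection rates rest on an assumed effect of 1 unit against a residual SD of 0.8, 40% compliance, an assumed spread of pace and assumed outcome return, and are illustrative only.

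It is not shown that the plan will read the wrong model term, or that minutes carry no information on engagement. Naming the term is a clarification to make at the same time. The point concerns one secondary analysis and leaves the primary analyses untouched.

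**What to change.** For the engagement analysis only:

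- Do not apply the content-compliance exclusion. Include everyone randomised to the two intervention arms who has outcome data; the attention-check rule can stay.
- Add content completed (0 to 15 modules and exercises) as an engagement measure beside minutes. The app already stores user inputs and usage.
- Name the term that answers the question: engagement × occasion (change from pre), or the post and follow-up scores adjusted for baseline, chosen in advance with the difference in Step 5 in mind.
- Report the result as an association, since engagement is not randomised.

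The cost is a change of wording and one more engagement measure. The analysis set will differ from that of the other analyses, and it gains only those non-compliers who still give outcomes. People who formally withdraw cannot be included, because the Recruitment Strategy section has their data destroyed.

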### Study Objectives

The scientific verification of processes that underpin several transdiagnostic maladaptive cognitive processes and psychopathological outcomes has several benefits. First, successfully identifying such processes advances the theoretical understanding of transdiagnostic processes themselves and their contributing roles in psychopathology. Second, it has the potential to improve several psychological treatment programs by identifying valuable targets for intervention [21], which is particularly valuable in treating cases of comorbidity. Using EMI and EMA in clinical trials offers a unique opportunity to evaluate the mechanisms underlying transdiagnostic processes that are difficult to assess through traditional self-report or laboratory methods (eg, avoidance). This study aims to examine whether the avoidance-focused EMI for rumination can modify the maladaptive feature of RNT, as understood through the link between daily RNT and well-being, depressive, and anxiety symptoms, compared with an active control group. We anticipate that the link between daily rumination and its maladaptive outcomes (lower well-being and higher depressive and anxiety symptoms) will be weaker in the intervention groups compared with the control group. Additionally, the study aims to confirm the role of avoidance in RNT.

Furthermore, by splitting the intervention condition into 2 groups (1 receiving concurrent therapist support and 1 not receiving concurrent therapist support), the study aims to evaluate whether intervention outcomes may be enhanced by the added availability of a supporting therapist [61].

Finally, the study aims to examine whether the impact of the avoidance-focused EMI for rumination on depressive and anxious symptoms can, compared with an active control group, be mediated by changes in beliefs about emotion (valuation of negative emotions) [62]. Similarly, the study aims to assess the EMI in terms of similar mediation effects of beliefs about rumination [63].

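### App time is named as a secondary outcome but used only as a covariate, and the therapist-support effect has no stated contrast free of that post-randomisation covariate

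*Protocol article*

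**What the plan says.** The Methods paragraph of the abstract reads "Secondary outcomes are the effects of a supporting therapist on postintervention outcomes in the intervention groups". It then adds app time as a second one, to represent engagement, and names a mixed-design ANCOVA as the method. Study Objectives gives the reason for splitting the intervention into two arms: "the study aims to evaluate whether intervention outcomes may be enhanced by the added availability of a supporting therapist". The Discussion (Study Strengths and Challenges) repeats that the standalone and supported versions will be compared.

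The Secondary Outcomes section of the statistical analysis says "Mixed-design analysis of covariance will be conducted within the 2 intervention groups", and the purpose it gives is "to examine whether time spent engaging with the app content serves as a covariate influencing intervention outcomes". The rest of that section concerns coding of qualitative user feedback.

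The Data Exclusion section adds that "the study will control for time spent within the app and the length of responses to open-ended questions", without limiting this to particular arms or analyses. The intervention section states that "the time taken to complete app content and assessments is also recorded to observe the time burden caused by app use", so the data exist.

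**The concern.** A variable announced as an outcome appears in the analysis section only on the right-hand side of the model. No section compares app time between the supported and unsupported arms, so the trial would report no engagement result of the kind the abstract announces. The coefficient for app time within these two arms is an observational association: people who use the app more differ from those who use it less in ways that randomisation does not balance.

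The therapist effect is the first-named secondary outcome, yet it is not mentioned in the section that sets the secondary analyses. The one model given for the two relevant arms conditions on app time. If support works partly by keeping people engaged, adjusting for engagement removes that part of its effect. The article itself makes this plausible, since the Discussion notes evidence that guided interventions may improve compliance. A reader of the results could then take a conditional effect for the benefit of adding a therapist.

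**Working it through.** **No figure in the plan to reproduce.** The article gives no effect size or precision for the support contrast or for app time. Its one design figure, a total of 60, is for four groups at three occasions and does not bear on this point.

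**Step 1: the role of app time in each place.**

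- Abstract, Methods: secondary outcome (measure of engagement), with ANCOVA named.
- Secondary Outcomes: covariate, two intervention arms.
- Data Exclusion: variable to control for, no arms or analyses specified.
- Development, Content, and User Evaluations: logged quantity, used to observe burden.

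No entry makes app time a dependent variable compared by arm.

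**Step 2: where the support effect could come from.**

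- Study Objectives and the Discussion state the comparison as an aim.
- Primary Outcomes gives a mixed-design ANOVA over all four conditions. Both intervention arms are in it, but no support contrast is named.
- Secondary Outcomes gives the two-arm ANCOVA. Support is the only planned difference between the arms, so the group term would be the support effect, conditional on app time.

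**Step 3: what conditioning on app time does.** Let T be the total effect of support on the post-intervention score (in SD, with benefit positive), a the effect of support on app time (in SD), and b the slope of outcome on app time within arm. With linear effects, no interaction and no unmeasured common cause of app time and outcome:

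adjusted group effect = T − a × b

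All values are assumed, because the article gives none. With T = 0.5:

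| a | b = 0.2 | b = 0.4 |
|---|---|---|
| 0 | 0.50 | 0.50 |
| 0.3 | 0.5 − 0.06 = 0.44 | 0.5 − 0.12 = 0.38 |
| 0.5 | 0.5 − 0.10 = 0.40 | 0.5 − 0.20 = 0.30 |
| 0.8 | 0.5 − 0.16 = 0.34 | 0.5 − 0.32 = 0.18 |

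A simulation of 200,000 observations per setting agreed to within 0.01 (for example 0.437 for a = 0.3, b = 0.2, and 0.173 for a = 0.8, b = 0.4). The unadjusted difference stayed between 0.49 and 0.51 throughout. The share of the total effect removed runs from 0.06/0.5 = 12% to 0.32/0.5 = 64%, and is zero when support does not change app time. If b were negative, adjustment would enlarge the effect instead. If motivation, say, drives both app time and outcome, adjustment can bias the contrast in either direction.

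In a repeated-measures model the same applies to the group-by-occasion term once app time is allowed to act on change. Time in the app accrues after baseline, so change is where any influence on outcome would have to appear.

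**Step 4: precision.** The target of 60 split equally gives 60/4 = 15 per arm. A two-sided 5% two-sample t test at one occasion then has power 0.26 for a 0.5 SD difference, and about 1.06 SD is detectable with 80% power. With 30 per arm the figures are 0.48 and 0.74 SD. Restating the contrast does not change this.

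**The case against.** The strongest reply is that the support effect can be obtained. A mixed design needs a between-subjects factor, and the only planned difference between the two arms is support, so group and group-by-occasion terms come with the ANCOVA. Both arms also sit in the four-condition ANOVA. An article may leave the exact contrast to an analysis plan that is not shown. This stands, and it rules out a reading that a reader might infer: that neither secondary outcome can be estimated. It does not remove the point. The section that fixes model, population and purpose names a different purpose, and its group term is conditional on app time.

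A reader might also infer that the Methods reverse a clear definition in the abstract, or change its scope. The documents do not support that. The abstract already names ANCOVA and is itself unclear on whether app time is outcome or covariate. For the therapist effect, both places refer to the intervention groups.

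A third tempting inference is that the article defines two different time quantities, one counting the daily assessments and one not. The wording does vary between app, app content and within the app. But the abstract is shorthand and never says that assessments count, and the sentence on recorded time describes logging for burden, not the engagement variable. No size can be put on this without assuming the minutes per assessment.

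Finally, comparing engagement by arm goes beyond the aim in Study Objectives, which concerns intervention outcomes. That is fair, but the abstract does list engagement as a secondary outcome.

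**Conclusion.** The point holds in this limited form. App time is listed as a secondary outcome but is used only as a covariate and a control variable, so it is not estimated as an outcome. The therapist-support effect has no stated contrast in the Secondary Outcomes section, and the model given there would return an effect conditional on a post-randomisation variable, not the total effect of support.

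The size depends on how far support changes engagement, which the article does not say. The attenuation worked out above is an illustration on assumed values, and it vanishes if support leaves app time unchanged. The general instruction in Data Exclusion carries the same problem into any randomised comparison to which it is applied, and length of open-ended responses is likewise a post-randomisation variable. With seven instruments in the pre-post battery and no named contrast, this should be settled before outcome data are seen.

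**What to change.** In Secondary Outcomes:

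1. State the support contrast: intervention with therapist support against intervention without it, on post-intervention scores, adjusted for the baseline score and any baseline covariates that the Study Design section brings in, but not for app time.
2. Define the engagement outcome as time on app content over the 4-week period, and compare it between the same two arms. Use the same definition in the abstract.
3. Keep the ANCOVA with app time as a predictor, labelled exploratory and non-randomised.

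In Data Exclusion, amend the sentence on control variables so that randomised comparisons are not adjusted for app time or response length. Without this change it would conflict with item 1.

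The cost is a few sentences and two two-group comparisons on data the app already logs, with no extra participants. The change fixes what is estimated. It does not improve the low power of the two-arm comparison, so the result should be reported as an estimate with its confidence interval.
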